## Abstract

**Background:**

Disconnected consciousness describes a state in which subjective experience (i.e., consciousness) becomes isolated from the external world. It appears frequently during sleep or sedation, when subjective experiences remain vivid but are unaffected by external stimuli. Traditional methods of differentiating connected and disconnected consciousness, such as relying on behavioral responsiveness or on post-anesthesia reports, have demonstrated limited accuracy: unresponsiveness has been shown to not necessarily equate to unconsciousness and amnesic effects of anesthesia and sleep can impair explicit recollection of events occurred during sleep/sedation. Due to these methodological challenges, our understanding of the neural mechanisms underlying sensory disconnection remains limited.

**Methods:**

To overcome these methodological challenges, we employ a distinctive strategy by combining a serial awakening paradigm with auditory stimulation during mild propofol sedation. While under sedation, participants are systematically exposed to auditory stimuli and questioned about their subjective experience (to assess consciousness) and their awareness of the sounds (to evaluate connectedness/disconnectedness from the environment). The data collected through interviews are used to categorize participants into connected and disconnected consciousness states. This method circumvents the requirement for responsiveness in assessing consciousness and mitigates amnesic effects of anesthesia as participants are questioned while still under sedation. Functional MRI data are concurrently collected to investigate cerebral activity patterns during connected and disconnected states, to elucidate sensory disconnection neural gating mechanisms. We examine whether this gating mechanism resides at the thalamic level or results from disruptions in information propagation to higher cortices. Furthermore, we explore the potential role of slow-wave activity (SWA) in inducing disconnected consciousness by quantifying high-frequency BOLD oscillations, a known correlate of slow-wave activity.

**Discussion:**

This study represents a notable advancement in the investigation of sensory disconnection. The serial awakening paradigm effectively mitigates amnesic effects by collecting reports immediately after regaining responsiveness, while still under sedation. Ultimately, this research holds the potential to understand how sensory gating is achieved at the neural level. These biomarkers might be relevant for the development of sensitive anesthesia monitoring to avoid intraoperative connected consciousness and for the assessment of patients suffering from pathologically reduced consciousness.

**Clinical trial registration:**

European Union Drug Regulating Authorities Clinical Trials Database (EudraCT), identifier 2020-003524-17.

## Introduction

1

During wakefulness, under normal conditions, our subjective experience (i.e., consciousness) is usually strongly influenced by external, environmental stimuli, that is, our consciousness is connected to the physical world [i.e., connected consciousness (CC)]. When transitioning to dream states (such as physiological dreaming or anesthesia-induced dreaming), our subjective experience often continues to be remarkably rich. Highly vivid sensory experiences during dreaming are frequently reported, yet they are usually unaffected by external stimuli, i.e., our consciousness is disconnected from the physical world [i.e., disconnected consciousness (DC)] (Figure 1). Corticocortical connections are functionally preserved to generate dreaming experiences, yet, somewhere in the thalamocortical stream, stimuli from the external world are blocked from conscious processing. Currently, a major obstacle to identify the cerebral gating mechanisms underlying sensory disconnection is the lack of behavioral differentiation between disconnected and connected conscious states in the neuroimaging literature. Previous research conducted on anesthetized participants has usually assumed a binary context, comparing brain activity acquired during wakefulness with brain activity acquired during presumed unconsciousness, where unconsciousness was inferred from participants’ unresponsiveness. Inferring the presence or absence of consciousness from (un)responsiveness^1^ has now been widely shown to be inaccurate, as unresponsiveness does not always correspond to unconsciousness (Sanders et al., 2012). Studies using the isolated forearm technique (i.e., assessing responsiveness by preventing muscle relaxants to act on one of the forearms) revealed in fact that up to 37% (Sanders et al., 2012; Linassi et al., 2018) of anesthetized patients, despite looking deeply asleep, were conscious of external stimuli (Sanders et al., 2012; Linassi et al., 2018). However, more recent estimates from clinical practice suggest that 5–10% of patients in routine clinical care experience these episodes (Sanders et al., 2017; Lennertz et al., 2023). Episodes of intraoperative dreaming are more frequent and have been estimated to occur in 22–59% of anesthetized, unresponsive patients (Leslie et al., 2007; Errando et al., 2008; Noreika et al., 2011). This implies that the supposed neural signature of consciousness gathered from classical anesthesia studies might conflate disconnected, connected consciousness, unconsciousness or the alternation between these states. We here propose that sensory perception of external stimuli can fluctuate while consciousness remains constant and independently of arousal (e.g., during dreaming), resulting in disconnected and connected dream-like experiences.

**Figure 1 fig1:**
[figure not shown]
Environmental (dis)connection and consciousness. Bubble clouds represent subjective experience [i.e., (un)consciousness]. **(A)** Connected consciousness during wakefulness: the boy’s subjective experience is strongly influenced by the surrounding environment. **(B)** Connected consciousness during dreaming: the subjective experience of the sleeping boy is partially influenced by the surrounding environment (the boy is dreaming of eating pizza) and, at the same time, sounds from the surrounding environment (in this case the cat’s sound) are incorporated into his experience. **(C)** Disconnected consciousness during dreaming: the boy’s subjective experience is not influenced by the surrounding environment (the boy is only dreaming about eating pizza, no environmental stimuli are incorporated into the ongoing experience). **(D)** Unconsciousness: the boy is devoid of any experience, whether originating internally or externally. Created with BioRender.com.

To disentangle between these different states and investigate the neural basis of (dis)connected consciousness,^2^ more recent studies have resorted to serial awakening paradigms during sedation (Radek et al., 2018; Scheinin et al., 2021; Casey et al., 2022a; Valli et al., 2023). With serial awakenings, participants are directly questioned about their mental activity that was ongoing before being awakened, minimizing the lack of explicit recall which is common due to amnesic effects of anesthesia or sleep (Siclari et al., 2013, 2017). However, contrasting episodes of (unresponsive) disconnected consciousness with other behavioral states [e.g., responsive wakefulness (Scheinin et al., 2021; Valli et al., 2023), self-reported wakefulness (Casey et al., 2022a)] impedes the segregation of the neural correlate of disconnected consciousness. Indeed, instead of reflecting the neural correlates of sensory (dis)connection, such contrasts could reflect differences in responsiveness or arousal system. A common assumption, also shared in these studies, is that connected consciousness is wakefulness, but this is not necessarily always the case, not least due to the complexity of defining wakefulness. There is evidence that during anesthesia patients often incorporate auditory and somatosensory stimuli into their dreams or perceive such stimuli in a dream-like state (Leslie et al., 2007, 2009; Leslie, 2010; Noreika et al., 2011; Radek et al., 2018). These episodes have been referred to as “near-miss awareness” (Leslie, 2010). Evidence that environmental stimuli can be perceived during dreaming without necessarily triggering wakefulness is also documented in sleep studies (Nielsen, 1993; Leslie and Ogilvie, 1996; Schredl et al., 2009). As the search for the neural correlates of consciousness (NCC) has been refined over the years by distilling the proper NCC from its prerequisites and consequences, the same should be attempted in the search for the NC of (dis)connected consciousness.

Although there is suggestive evidence indicating that a breakdown in cortical effective connectivity (Massimini et al., 2005) might underlie the loss of consciousness in anesthesia (Boly et al., 2012) and sleep (Esser et al., 2009), the challenge heightens when attempting to pinpoint the specific mechanism responsible for the loss of environmental connection during these states. While we know that sensory stimuli reach primary sensory regions during presumed unconscious and dream states, it is unknown how they are processed in disconnected states in both primary and secondary regions. In REM sleep (Funk et al., 2016) and mild sedation with propofol (Boly et al., 2012), deactivation of primary areas has been shown to coexist with the activation of secondary/associative regions, favoring top-down over bottom-up cortical signaling. This imbalance between top-down/bottom-up information flow may be one of the potential mechanism for the decoupling of consciousness from environmental connection (Murphy et al., 2011; Funk et al., 2016; Andrillon and Kouider, 2020; Casey et al., 2022b). Recent studies also suggest a role in disconnectedness for specific thalamic nuclei, depressing cortical function and compromising thalamocortical information flow (Liu et al., 2015; Feng et al., 2017). Finally, a mechanistic role for local slow wave activity (SWA)–δ band (1–4 Hz) frequency oscillations—has been proposed for inducing disconnectedness. Local SWA has been found in all those states that present episodic coupling of conscious experience with disconnection from the environment: SWA was recorded during REM sleep at the level of primary sensory and motor cortices (Funk et al., 2016) and has long been found in NREM sleep and anesthesia (Murphy et al., 2011). In propofol anesthesia, SWA saturation has been reported to deactivate the thalamus and primary cortices, interrupting wake-like brain activity to external stimuli, thus probably inducing a state of disconnectedness (Mhuircheartaigh et al., 2013).

Here, we propose to identify unresponsive connected and disconnected dream-like states by delivering auditory stimuli during propofol-induced mild sedation and serially awaking healthy participants. We will collect subjective reports about mental activity prior to awakening (assessing dreaming/consciousness) and stimulus perception (assessing connectedness), while ensuring unresponsiveness throughout the experiment and minimizing the risk of arousals. The cerebral activity of participants will be recorded by means of functional MRI. During the auditory stimulation session, we will play series of sounds following the oddball rule, in which trains of beeps of the same frequency (i.e., standard sounds) are occasionally interrupted by a beep of a different frequency (i.e., the deviant or “oddball” sound). This way, we will be able to investigate not only the difference in the perception of sounds during connected and disconnected consciousness, but also whether standard and deviant sounds are processed differently in the two conditions.

Capitalizing on the enhanced spatial resolution of BOLD fMRI, we will (1) characterize stimulus processing within several thalamic nuclei, and primary and secondary cortices during connected (CC) and disconnected consciousness (DC). To this end, we will conduct a hypothesis-driven ROI analysis, in which we will test various hypotheses on the involvement of thalamic nuclei (*Hypothesis 1*), primary auditory cortex (*Hypothesis 2*) and secondary areas (*Hypothesis 3*) in the processing of auditory stimuli during CC and DC states. The ROI analysis will be complemented by an exploratory whole-brain analysis aimed at identifying other regions potentially involved in sensory disconnection. If *Hypothesis 1–2* prove true, it would indicate that already at a basic level of stimulus processing there is a difference between CC and DC. To investigate this further, we aim (2) to characterize changes in functional connectivity between the thalamus and primary auditory cortices with the rest of the brain in CC and DC. We hypothesize (*Hypothesis 4*) that the functional connectivity between the thalamus [e.g., the pulvinar (Kanai et al., 2015; Sanders et al., 2021)] and primary auditory cortices will be stronger in CC compared to DC. If this hypothesis is confirmed (together with Hypothesis 1–2) it would suggest that some gating mechanism already occurs at the thalamic level. However, this difference in brain activity might be necessary but not sufficient to cause sensory disconnection: that is, a weakened connection between the thalamus and primary auditory cortices does not imply that sensory stimuli are *entirely* blocked from cortical processing via the gating action of the thalamus [thalamic gate hypothesis (Andrillon and Kouider, 2020)]. It would however indicate that differential processing of stimuli in CC and DC already occurs at the thalamic level. This thalamic modulation of sensory inputs could in turn affect cortical processing, leading to a cortical gate, that is, loss of information propagation to higher cortices due to a disruption in functional connectivity (cortical gating hypothesis). In this respect, we hypothesize (*Hypothesis 5*) that the functional connectivity between primary and secondary auditory cortices will be stronger in CC compared to DC. Voxel-to-voxel functional connectivity analysis will be conducted for standard and deviant sounds separately: we hypothesize (*Hypothesis 6*) that different processing for deviant and standard sounds will be present in CC but absent in DC. Finally, we aim (3) to quantify high-frequency BOLD oscillations, which have been shown to track sleep slow waves (Song et al., 2022), in selected thalamic nuclei and in primary and secondary cortices. We hypothesize (*Hypothesis 7*) that high-frequency BOLD oscillations will be lower in high-order/first-order thalamic nuclei and in primary and secondary sensory cortices during CC compared to DC.

In summary, we propose an fMRI experiment that systematically differentiates connected and disconnected conscious states by delivering auditory stimuli and serially awakening participants sedated with propofol to assess the conscious state and stimulus perception through subjective reports. Through activation and connectivity analyses of collected fMRI data, we will investigate whether sensory disconnection is caused by altered activity at the level of thalamus, primary regions, or, higher up, due to a lack of stimulus integration in associative areas. This project will provide fundamental insights on the neural correlates of sensory disconnection.

## Methods

2

### Inclusion and exclusion criteria

2.1

Participants will be screened through an online form, an in-person interview and a medical examination. The initial phase of screening using the online form will select healthy, right-handed, non-smoking, MRI-compatible subjects without psychiatric and neurological disorders, propensity for nausea, recurrent nightmares, memory and hearing impairments, substance abuse, cannabis use in the three months preceding the study and regular alcohol consumption (i.e., everyday). During the in-person interview it will be verified that the above inclusion/exclusion criteria are fulfilled to avoid oversights or errors in filling out the form. Furthermore, we will select participants who have a low risk of obstructive sleep apnea through the StopBang questionnaire (Low Risk: Yes to 0–2 questions) (Chung et al., 2008, 2012) and low levels of anxiety through the scales “Novelty Seeking” and “Harm Avoidance” of the Temperament and Character Inventory self-rating questionnaire (Cloninger et al., 1993). We will only include participants with average or above average scores on the “Novelty Seeking” scale (i.e., ≥16.5 for men and ≥ 16.3 for women) and participants with average or below average scores on the “Harm Avoidance” scale (i.e., ≥14.5 for men and ≥ 17.5 for women) (Pélissolo and Lépine, 2000). We control for obstructive sleep apnea because of the known respiratory depression effects of propofol. We take into account the predisposition to anxiety as anxious participants might require higher propofol concentrations to achieve loss of responsiveness compared to non-anxious participants, impairing subsequent recovery of responsiveness and report collection. Participants who meet these criteria will be visited by an anesthesiologist with an evaluation similar to a pre-surgical examination, including a physical examination, full review of the patient’s medical, surgical and allergological history, treatment and intubation score and any potential contraindication to propofol sedation. Finally, alcohol consumption will be forbidden for 48 h preceding the experiment. A proper sleep hygiene is encouraged in the 2 to 3 days prior to the study. Participants are required to refrain from drinking and eating six hours before the start of the experiment.

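### The Harm Avoidance cut-offs carry the wrong inequality sign, so the numeric rule admits the higher-scoring volunteers that the worded rule excludes

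*Protocol article*

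**What the plan says.** Section 2.1 (Inclusion and exclusion criteria) of the protocol article uses two temperament scales to choose volunteers with "low levels of anxiety through the scales “Novelty Seeking” and “Harm Avoidance” of the Temperament and Character Inventory self-rating questionnaire". Each scale has a rule in words followed by a numeric version in brackets.

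- Novelty Seeking: "average or above average scores on the “Novelty Seeking” scale (i.e., ≥16.5 for men and ≥ 16.3 for women").
- Harm Avoidance: "participants with average or below average scores on the “Harm Avoidance” scale (i.e., ≥14.5 for men and ≥ 17.5 for women").

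The section then gives its reason for screening on anxiety: "anxious participants might require higher propofol concentrations to achieve loss of responsiveness compared to non-anxious participants". It adds that this would hamper the later return of responsiveness and the collection of reports. The Harm Avoidance cut-off is not restated or corrected anywhere else in the article.

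**The concern.** The bracketed numbers are introduced as a restatement of the words, but they point the other way. Cut-offs are what a person scoring a questionnaire applies, and what another group would copy to repeat the study. If the printed numbers were used, the screen would work against its own purpose on this scale.

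By the article's own reasoning, that could affect the trial in two places. The connected or disconnected condition comes entirely from reports given after awakening (section 2.3), so a participant who cannot be roused or understood yields no classifiable session. Propofol concentration is also a fixed effect in the group-level model (section 2.9.5), and its distribution could shift with the kind of volunteer enrolled.

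**Working it through.** No formula is involved and the plan states no figure to reproduce. The check sets the words, the sign, the parallel rule and the stated purpose side by side, all from section 2.1.

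| Scale | Direction in words | Printed cut-offs (men / women) | Direction of the sign | Agree? |
|---|---|---|---|---|
| Novelty Seeking | average or higher | ≥16.5 / ≥16.3 | average or higher | yes |
| Harm Avoidance | average or lower | ≥14.5 / ≥17.5 | average or higher | no |

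**Step 1: how far the two Harm Avoidance rules overlap.** For men, the words admit scores of 14.5 or less and the numbers admit scores of 14.5 or more. The only score in both sets is 14.5. For women, by the same reasoning, it is 17.5. If the scale gives whole-number scores only (the article does not say), no volunteer can score either value and the two rules never admit the same person.

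**Step 2: illustration.** These scores are invented to show the effect and do not come from the article.

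| Volunteer | Score | By the words | By the numbers |
|---|---|---|---|
| Man | 10 | eligible | excluded |
| Man | 20 | excluded | eligible |
| Woman | 12 | eligible | excluded |
| Woman | 25 | excluded | eligible |

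Every decision is reversed.

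**Step 3: which part is wrong.** Three things in the section support the words. The stated aim is low anxiety. The rationale treats anxious volunteers as the ones to avoid. And the same sign already expresses the opposite direction, correctly, for Novelty Seeking. Nothing in the section supports the sign.

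**Step 4: how much room the design has if the numbers were applied.** Section 2.8 takes 74 sessions as the requirement, allows 8% dropout with failure to lose or regain responsiveness as the example, and plans 80 sessions (40 subjects × 2). The expected yield is 80 × 0.92 = 73.6 sessions, against 74 required. The allowance is therefore fully used before any additional failed awakenings. This shows only that there is no slack. It does not estimate how many more failures a reversed screen would cause, and the article gives no basis for such an estimate.

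**The case against.** The strongest reply is that this is a slip in a bracket. The worded criterion is correct, the section signals the intended direction three times, and a careful reader can recover the meaning. The sign was probably carried over from the Novelty Seeking cut-offs, and screening may well have followed the words. The screening form and the full protocol are not shown, so it cannot be assumed that either contains the error.

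The consequences are also conditional. The article says only that anxious participants might need higher concentrations. Each participant is titrated individually, a training session adjusts the concentration so that intelligible reports can be obtained (section 2.2), and the group model adjusts for concentration. Entrants must in any case meet the Novelty Seeking rule and have no psychiatric disorder, so those admitted by the reversed numbers would be average or higher on one scale, not anxious in every sense. No hypothesis, model or sample-size figure changes.

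Most of this stands, and it limits what can be claimed about harm. It does not remove the contradiction. Titration and covariate adjustment do not restore the intended population, and a meaning that can be inferred does not make a numeric eligibility threshold correct.

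**Conclusion.** The criterion is wrong as written. On Harm Avoidance, the numeric version describes the opposite population from the worded one, and the two share at most a score exactly at the cut-off. The section's own aim and rationale show that the sign is at fault.

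This conclusion rests on the text of one section and on no outside source. Whether 14.5 and 17.5 are the right published averages cannot be checked from the article, and the point does not depend on it. Any effect on failed awakenings, lost reports or propofol concentration depends on the printed numbers having been used in screening, and its size is unknown. If screening followed the words, the damage is confined to the published text.

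**What to change.** Change the Harm Avoidance cut-offs in section 2.1 to ≤14.5 for men and ≤17.5 for women, so that the numbers match the stated rule. Confirm which direction the screening form and the full protocol use, and correct them if they carry the same sign. Check the screening log for volunteers already assessed. If any were admitted or refused on the reversed rule, report how many.

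The cost is two symbols and one pass through the log. No analysis, sample size or schedule has to change.
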